### Data collection

Data will be collected in form of self-filled paper-and-pencil questionnaires and in form of physical activity assessments by research assistants who are blinded to group allocation and will go through a profound assessment training program. Success of blinding will be estimated by asking the research assistants to guess the allocation of the study groups after every measurement and comparing the answers with what would be expected by chance [27]. Unblinded assessors will be replaced by another trained, blinded researcher whenever possible. Otherwise, loss of blinding will be recorded and considered in the analysis. Data collection with patients will take place in the patients’ home. Only pseudonymised data will be collected and every cluster, PT and home care nurse will receive a pseudonymised code. Interviews with all participants will be conducted by telephone and tape-recorded.

### Data management

We created a concept for data protection in cooperation with both data protection officials in both study sites that is based on the EU General Data Protection Regulation (EU-GDPR) and federal legislation. Only the responsible researchers will have access to the pseudonym data sets. The data will be encrypted and password-protected when being transferred between secure servers. Data managers and biostatisticians will receive the original paper-based pseudonymised questionnaires. Two research assistants of their team will check the data for inconsistency and completeness and then entered into a database and validated through double entry so that the biostatistician can analyse data without having access to information about the allocation. The pseudonymised data will be handled and stored according to the data protection declaration of the institution. Tape-recorded qualitative data from interviews will be transcribed verbatim and afterwards the audio file will be deleted.

### Data analysis

The data analysis of the measured outcomes will be done by a blinded biostatistician who is not involved in the study. The primary analysis will be based on a linear mixed model of the DHI changes between t_0_ and t_2_, using intervention group and initial DHI as fixed factors and a random intercept for cluster. The statistical inference will be based on the Wald *t*-test for the intervention on an alpha level of 5% (two-sided). Similar models will be applied for exploratory analyses of the secondary outcomes. No pre-specified subgroup analyses are planned. Due to the restricted sample size, no additional adjustments for other fixed effects are planned. Range and cross-checks of the outcome variables and key baseline patient characteristics will be performed. Impossible or implausible data will trigger queries to the team of the principal investigator. All analyses will be based on the intention-to-treat principle. In case of dropouts, the last available observation will be carried forward. No interim analyses are planned.

For the process evaluation, quantitative data will be analysed descriptively. Qualitative data from interviews and field notes from research team, GPs and PTs will be analysed with content analysis [50], which will be performed by two independent researchers from the study centres.

To analyse the cost-effectiveness of the intervention, an incremental cost-effectiveness ratio and an incremental cost-utility ratio will be calculated as the ratio of the difference in mean cost and the difference in mean health effects (DHI or QALY) between study groups during the 6-month follow-up period. Non-parametric bootstrap method will be employed to generate confidence intervals around the difference in mean cost and the difference in mean health effects. Uncertainty surrounding the cost-effectiveness ratio and cost-utility ratio will be presented on the cost-effectiveness plane. Furthermore, cost-effectiveness acceptability curves, based on the incremental net-monetary benefit will be constructed. The study will be terminated when all collected data have been analysed and utilised within the analysis plan.

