#### Secondary objectives

Secondary outcomes are physical activity, static and dynamic balance, falls and fear of falling as well as quality of life. We will also evaluate the safety in terms of falls. Cost-effectiveness and cost-utility of the CPW will be assessed in a health economic evaluation alongside the trial. To understand the behaviour change process, as well as barriers and facilitating aspects of implementation, the study will be accompanied by a comprehensive process evaluation.

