### Intervention

#### Experimental intervention

The intervention is an algorithmized evidence-based multidisciplinary CPW to enhance the care of older persons with VDB and thus promote their mobility and participation in daily living. It illustrates all steps of the patient pathway through a standardised approach consisting of two main components:A paper-based *checklist for standardise clinical decision making*, which contains evidence-based diagnostics, treatment and referral options for the whole treatment period and is applied by previously trained GP. The aim of the checklist is to help the GP to make a classifying diagnosis, to guide the next steps and to prioritise them.A *decision tree* for evidence-based physiotherapeutic clinical reasoning and treatment of VDB. It consists of recommendations and options for anamnesis (including information about clinical pattern), specific assessments, treatment and evaluation. The decision tree will be applied by previously trained PT, if the treating GP prescribes physiotherapy.

At the beginning of the 4-month intervention period, the patients make an appointment with their GP who performs the anamnesis and the examinations based on the checklist. The anamnesis involves questions regarding the quality, character, frequency and duration of VDB and accompanying symptoms. Then, further examinations like position manoeuvre and neurological tests will be undertaken by the GP. Depending on the results of the anamnesis and examinations, the checklist contains suggestions for further referral and treatment (see Fig. 2). Referral suggestions can be the referral to a neurologist, otorhinolaryngologist, internist/cardiologist and PT. Treatment options may include symptomatic bridging therapy with medication or general treatments such as medication adjustment. The treatment by and therefore the referral to a trained PT is recommended when the checklist/GP comes to the following conclusions: the patient suffers from benign paroxysmal positional vertigo, other factors requiring examination by another physician specialist can be excluded and/or has taken place before with no results.

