##### Safety

Falls during the intervention period could be a possible risk or complication. The incidence of falls during the intervention period as main safety outcome will be documented in the physical activity diary. Additionally, falls within the last 6 months before the start of the intervention will be assessed.

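### The model stated for secondary outcomes, a linear model of change with carry-forward, does not estimate the incidence of falls, the main safety outcome

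*Protocol article*

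**What the plan says.** All references are to the protocol article.

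- **Role of falls.** The Primary objective covers effectiveness and safety. Under Secondary objectives: "Secondary outcomes are physical activity, static and dynamic balance, falls and fear of falling as well as quality of life".
- **Follow-up measure** (Safety): "The incidence of falls during the intervention period as main safety outcome will be documented in the physical activity diary". Experimental intervention gives the length of that period: "At the beginning of the 4-month intervention period".
- **Baseline measure** (Safety): "falls within the last 6 months before the start of the intervention will be assessed".
- **Model** (Data analysis): "The primary analysis will be based on a linear mixed model of the DHI changes" from t0 to t2, with group and initial DHI as fixed factors and a random intercept for cluster. For everything else: "Similar models will be applied for exploratory analyses of the secondary outcomes". No other fixed effects are planned.
- **Missing data** (Data analysis): last observation carried forward for dropouts. Falls are not exempted.
- **Observation of falls.** Sample size allows for 23% dropout. Recruitment has home care services informed for intervention patients only. According to the Discussion, the pocket card given to these services includes a reminder to fill in the activity diary.

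No count model, observation time or separate analysis is named for falls.

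**The concern.** The Safety section promises an incidence, which is events per unit of time observed. The only model described is a difference in change scores with no time in it. Read literally, it fits falls badly in four ways.

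- The change would subtract a 6-month count from a 4-month count.
- The model's t0 to t2 interval is 6 months, whereas falls are defined over the 4-month intervention period.
- A diary that stops early counts as fall-free for the weeks not recorded.
- For a patient with no diary data, the only falls value to carry forward is the 6-month pre-trial count.

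At stake is the trial's main safety comparison. If one arm is observed for longer, it records more falls at the same rate. This could look like harm or hide a benefit.

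**Working it through.** The article gives no fall rate, power or sample size for falls, so there is no printed figure to reproduce. Fall rates, dispersion and stopping proportions below are assumptions. The 6-month and 4-month windows and the total of 120 patients (60 per arm at 1:1) come from the protocol.

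**1. Windows within an arm.** At 0.12 falls per patient-month with no real change, the expected counts are 0.12 × 6 = 0.72 at baseline and 0.12 × 4 = 0.48 in follow-up. The apparent drop is 1 − 4/6 = 33%. In general the expected change is −2 × rate, or −0.10 to −0.40 falls at 0.05 to 0.2 per month.

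**2. Windows between arms.** Let Y be the follow-up count, B the baseline count and G the group. The model Y − B = a + τG + βB + e is the same as Y = a + τG + (β + 1)B + e. The group coefficient τ is identical. The subtraction, and with it the 33%, therefore drops out of the arm contrast.

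**3. Unequal diary time.** Suppose 15% of intervention and 30% of control patients stop the diary at a time uniform over 4 months, with the same fall rate in both arms. The average is (15 + 30)/2 = 22.5%, close to the planned 23% dropout. Mean diary time is 4 × (1 − 0.15 × 0.5) = 3.7 months against 4 × (1 − 0.30 × 0.5) = 3.4 months.

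| Rule | Ratio, intervention to control | Arms swapped |
|---|---|---|
| Partial count taken as complete | 0.925/0.85 = 1.09 | 0.92 |
| 6-month baseline carried forward for every stopper | (0.85 × 4 + 0.15 × 6)/(0.70 × 4 + 0.30 × 6) = 4.3/4.6 = 0.93 | 1.07 |
| Rate over observed time | 1.00 | 1.00 |

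These ratios do not depend on the fall rate. Simulation (60 per arm, gamma-Poisson with k = 0.5, 4,000 runs) gave 1.092, 0.936 and 1.002 for the first column. As a difference in mean counts, either rule gives 0.3 × rate in absolute value: 0.015 to 0.06 falls at 0.05 to 0.2 per month. With equal stopping in both arms, every ratio is 1.00.

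**4. Size against sampling error.** With mean 0.48, k = 0.5 and 60 per arm, the SE of the log ratio is √[2 × (0.48 + 0.48²/0.5)/(60 × 0.48²)] = 0.37 before clustering. The bias is ln(1.088) = 0.084, and 0.084/0.37 = 0.23 SE. Two-sided rejection under the null rises from 5% to about 5.6%.

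**5. A larger gap.** A second simulation used 120 patients, dispersion 1, no cluster effect, rates of 0.05 to 0.2 per month and 1,500 runs per setting. It compared the linear change model with a rate over diary time.

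- Equal diary time, no effect: the linear difference is about 0 and rejection is 4% to 6%.
- Control 4 months, intervention 3, no effect: −0.05 to −0.20 falls, rejection 10% to 19%.
- Control 3 months, intervention 4, no effect: +0.05 to +0.20 falls, rejection 9% to 20%.
- True rate ratio 0.7, intervention 4 months, control 3: the raw count ratio is 0.7 × 4/3 = 0.93, so the benefit is almost hidden.
- The rate over diary time gave 0.96 to 1.03 when the truth was 1.0, and 0.67 to 0.71 when it was 0.7.

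These settings shorten every diary in one arm by a month, a far wider gap than in step 3.

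**The case against.** The strongest reply is that the text says similar models, not the same one. A count model with group, baseline falls and a random intercept for practice could be called similar. Distribution and offset are details that an article may leave to an analysis plan, the analyses are labelled exploratory, and the word incidence already points to a rate. This has weight and limits the importance of the point. It does not remove it: the only model described is linear and for change, and the carry-forward rule is stated without exception.

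A reader might infer more than the documents support:

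- **That the falls estimate reflects diary length and not fall rate.** With equal diary time in both arms, the linear contrast still reflects the fall rate (working, steps 2 and 5).
- **That the 33% drop is a false treatment effect.** It occurs within each arm, and the planned test is of the group term only.
- **That diaries are known to be incomplete.** The missing values reported in the Discussion concern the activity questionnaire and the StepWatch device. The diary was revised and patients are to be helped with it.
- **That carry-forward of pre-trial counts is planned.** This follows only if the general rule is applied to falls as written.

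The concern that diary time may differ by arm still stands. Help from the study team is general, but the home-care reminders are one-sided. The share of patients receiving home care is not given.

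**Conclusion.** The point holds in a limited form. As written, the analysis of the main safety outcome does not estimate the incidence that the Safety section names: it has no observation time, and its carry-forward rule can mix a 6-month and a 4-month count. The arm contrast is biased only if diary time or dropout differs between arms. This is plausible from the planned 23% dropout and the one-sided reminders, but it is not documented. With assumed stopping of 15% against 30%, the distortion is modest, a ratio of about 0.92 to 1.09. Its direction depends on which arm stops more and which rule is used, and at about 0.23 SE it is well inside the sampling error. It becomes material only if diary time differs by something like a month throughout an arm.

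**What to change.** In Data analysis, except falls from both the similar-models sentence and the carry-forward rule. Analyse the number of falls in the intervention period with a negative binomial mixed model: log of observed diary days as offset, arm and baseline falls (6-month count) as covariates, and a random intercept for practice. Report the rate ratio with its 95% CI. Compute no change score; each patient contributes the days observed. Report diary days by arm, so that any imbalance is visible.

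The cost is a sentence or two and standard code. Diary start and stop dates must be recorded. With 12 clusters and perhaps few falls, a simpler variance structure may be needed. The rate model also assumes that stopping the diary is unrelated to fall risk, given the model terms; it corrects for time not observed, not for selective stopping.

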### Sample size

Sample size calculation was informed by data of a cohort study with the same population [32]. Data gave evidence of an ICC = 0.04 and an expected standard deviation of 25. A cluster size of 10 is assumed, i.e. the variance inflation factor is 1 + (10 − 1) × 0.04 = 1.36. The study plans to detect a score difference between intervention groups of at least 12 points [30] on a two-sided alpha level of 0.05 with a power of 80%, resulting in a total sample size of ((1.96 + 0.84)^2^ × 2 × 25^2^ × 1.36)/12^2^ = 92.6. Recruitment of 12 clusters à 10 patients accounts for a dropout rate of 23%. The study will be conducted in two waves, resulting in six clusters (three per study centre) à ten patients being recruited per wave. Current experience shows that a few clusters will possibly fail to recruit the necessary number of patients. In this case, we will recruit more patients in other clusters to compensate for this. To maintain the statistical power of the study, the following rule will be applied: number of patients to be additionally recruited in other clusters = 1.5 × number of patients that some clusters fail to recruit.

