### Allocation

GP practices will be randomly allocated to the intervention or control group after written informed consent. Stratified block randomisation by region (two times three clusters in Saxony, two times in south-eastern Bavaria) will be used. The block length will be two, ensuring an equal number of clusters providing the experimental and the control intervention, respectively. The most recent version of the Statistical Analysis System SAS (SAS Institute, Cary, NC, USA) will be used for generating the sequence. Allocation will not and cannot be concealed from the members of the research team distributing the study materials to the care providers. The allocation sequence will be generated by a statistician who is not involved in the study.

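### Randomisation is stratified by region but the primary model leaves region out; if the regions differ in DHI change, the standard error is overstated and precision is lost

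*Protocol article*

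**What the plan says.** Under Allocation, the protocol article states: "Stratified block randomisation by region (two times three clusters in Saxony, two times in south-eastern Bavaria) will be used". It adds: "The block length will be two, ensuring an equal number of clusters providing the experimental and the control intervention, respectively". Sample size plans three practices per study centre in each of two waves, so six practices per region and twelve in all.

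Under Data analysis, the primary model is a linear mixed model of DHI change from baseline to 6 months, "using intervention group and initial DHI as fixed factors and a random intercept for cluster". The treatment effect is tested with a Wald t-test "on an alpha level of 5% (two-sided)". The list of terms is then closed: "Due to the restricted sample size, no additional adjustments for other fixed effects are planned". Models of the same kind are planned for the secondary outcomes.

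Region is therefore the named stratification factor of the design, and the stated analysis leaves it out. This is an expressed choice, not a detail that the article leaves to a fuller document.

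**The concern.** Blocks of two within region balance the arms inside each region, so a difference between Saxony and south-eastern Bavaria cancels from the arm comparison. A model without region cannot know this. It sees practices in one region lying above those in the other and attributes the gap to random practice variation. The estimated between-practice variance rises, and with it the standard error of the treatment effect. The design obtains a gain in precision that the analysis then does not use.

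With only 12 practices, the precision of the comparison depends heavily on how practice means vary. Region also coincides with study centre, so it could carry differences in centre procedures as well as in patients. The stated reason, a restricted sample size, is a good argument against a long list of covariates. It is a weaker one against a single two-level factor used in the randomisation.

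**Working it through.** **Inputs** (Sample size and Allocation): SD 25; ICC 0.04; 10 patients per practice; 12 practices, 6 per arm and 6 per region; target "a score difference between intervention groups of at least 12 points", "on a two-sided alpha level of 0.05 with a power of 80"%. The protocol gives no regional difference in DHI change, so D is varied.

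**Assumptions.** The SD and ICC apply to the baseline-adjusted change. The blocks run on across both waves, so each region ends with three practices per arm. Practices are of equal size.

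**The plan's own figure.** (1.96 + 0.84)² × 2 × 25² × 1.36 / 12² = 92.56, which matches the printed 92.6. This expression gives a number per arm, although it is labelled a total. That is a separate matter. It is mentioned only because it explains why the power figures below lie near 50% and not 80%.

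**Variance of a practice mean.** Between practices: 0.04 × 625 = 25. Within: 600/10 = 60. Total: V = 85.

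**With region in the model.** SE = √(85 × 2/6) = √28.33 = 5.32, whatever D is, on 9 between-cluster df.

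**Without region.** Each practice lies D/2 above or below the overall mean because of its region. This adds 12 × (D/2)² = 3D² to the between-practice sum of squares. On 10 df the variance estimate averages 85 + 0.3D², so SE = √((85 + 0.3D²)/3).

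The table compares the two models. Half-widths use t = 2.228 (10 df) without region and 2.262 (9 df) with region. Power is for 12 points, from the t distribution with region and by simulation without.

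| D | SE without region | Excess over 5.32 | 95% half-width without / with | Power without / with |
|---|---|---|---|---|
| 0 | 5.32 | 0% | 11.86 / 12.04 | 53.0% / 52.1% |
| 3 | 5.41 | 1.6% | 12.05 / 12.04 | 51.9% / 52.1% |
| 5 | 5.55 | 4.3% | 12.37 / 12.04 | 49.7% / 52.1% |
| 8 | 5.89 | 10.7% | 13.13 / 12.04 | 44.9% / 52.1% |
| 10 | 6.19 | 16.3% | 13.80 / 12.04 | 40.7% / 52.1% |

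**Break-even on interval width.** Set 0.3D² = 85 × ((2.262/2.228)² − 1) = 85 × 0.0308 = 2.61. This gives D ≈ 2.95.

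**After the planned dropout** (92.6/12 ≈ 7.7 patients per practice), the excess is 1.3% at D = 3, 3.6% at D = 5 and 13.7% at D = 10. Break-even is about 3.2 points.

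**If D is already inside the stated ICC**, the variance between practices within a region is 25 − D²/4.
- D = 5: V = 18.75 + 60 = 78.75. SE is 5.12 with region and √((78.75 + 7.5)/3) = 5.36 without, an excess of 4.7%. Power is 55.2% with and 52.6% without.
- D = 10: V = 60. SE is 4.47 with region and √(90/3) = 5.48 without, an excess of 22.5%. Power is 66.7% with and 50.6% without.

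**The case against.** **The consequence is conditional.** The strongest reply is that the standard error is overstated only if baseline-adjusted DHI change differs between regions, and nothing in the protocol gives or suggests such a difference. Adjustment for initial DHI already absorbs regional differences in starting severity. Below about 3 points the region term does not narrow the interval, and with no difference it costs about one point of power. On that view, keeping the model small is defensible. This stands, and it limits the point to a conditional loss of precision.

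**The larger scenarios strain the plan's inputs.** A stated between-practice variance of 25 means an SD of 5 points. If that variance includes region, D = 8 would use 64/4 = 16 of the 25, and D = 10 would use all of it. If D is additional, D = 10 adds 100/4 = 25 and so doubles the between-practice variance. The protocol does not say which applies. This also stands: D = 8 and D = 10 are outer cases, and D = 5, with a power difference of 2.4 to 2.6 points, is the more moderate one.

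**A reader might infer that the planned test is conservative.** The protocol does not support that without qualification, because the Wald t-test is named without its degrees of freedom. With 10 df and an unconstrained practice variance, actual alpha without region would be 0.047 at D = 3 and 0.042 at D = 5. With large-sample df and the practice variance held at or above zero, simulation of the same balanced layout gives 0.060 at D = 0, 0.058 at D = 3 and 0.054 at D = 5, all above 5%. For modest D, the choice of df governs calibration more than the region term does.

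**A reader might also infer bias, or blame this omission for the low power.** Neither follows. Stratification keeps the estimate unbiased under balance, and the low power comes from the sample-size calculation.

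**Conclusion.** The omission is certain, since the model is fully listed and further fixed effects are excluded. Its effect is conditional. If the regions differ by D points in baseline-adjusted DHI change, the standard error is overstated by about 1.6% at D = 3, 4.3% at D = 5, 10.7% at D = 8 and 16.3% at D = 10, with D additional to the stated ICC. If the regions do not differ, nothing is lost by leaving region out.

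These figures rest on the protocol's SD, ICC and practice size, equal practices, and three practices per arm in each region. The plan to make up shortfalls by recruiting more patients in other practices could leave region unbalanced by arm at patient level; a region term would adjust for that too.

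The stated reason does not weigh the two sides well. Inclusion costs at most about one point of power, while the loss from omission grows with D. This is a cheap improvement and not a flaw that endangers the conclusion.

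**What to change.** Add region (two levels) as a fixed effect to the primary model and to the parallel models for the secondary outcomes. State that the Wald t-test uses between-cluster, small-sample degrees of freedom. Amend the closing sentence to: *no adjustment beyond baseline value and the stratification factor region*. Make the change before the allocation is disclosed to the analyst.

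The cost is one model term and one of about ten between-cluster degrees of freedom. The critical t moves from 2.228 to 2.262 (+1.5%), and power falls from 53.0% to 52.1% if the regions do not differ. The change pays for itself once the regional difference exceeds about 3 points. It needs no new data and no change to the randomisation.

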### Outcomes

The primary and secondary outcome will be assessed on patient level in the intervention group and control group at three measurement points: at baseline before the intervention (*t*_0_), after 4 months (*t*_1_) and after 6 months (*t*_2_). Additional data on GP practices, PT practices and home care nursing services level will be assessed at *t*_0._ For an overview of the research outcomes and assessments, see Table 2.

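### Last observation carried forward is the only dropout rule for the primary DHI analysis; it biases the 6-month effect by an amount and in a direction set by when and in which arm patients leave

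*Protocol article*

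**What the plan says.** In the protocol article, Data analysis, the primary model takes each patient's DHI change from baseline to the 6-month visit as its outcome. Its terms are given as "using intervention group and initial DHI as fixed factors and a random intercept for cluster". The same paragraph adds "All analyses will be based on the intention-to-treat principle" and then "In case of dropouts, the last available observation will be carried forward". It names no other method for missing data and no sensitivity analysis.

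Under Outcomes: "The primary and secondary outcome will be assessed on patient level in the intervention group and control group at three measurement points", namely baseline (t0), 4 months (t1) and 6 months (t2). The intervention period is 4 months, so t1 falls at its end and t2 two months later.

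Under Sample size: "The study plans to detect a score difference between intervention groups of at least 12 points", and "Recruitment of 12 clusters à 10 patients accounts for a dropout rate of 23" per cent.

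**The concern.** With only three visits, carrying forward does one of two things. A patient lost before t1 has only the baseline value, so the primary outcome becomes t0 minus t0, which is exactly zero. A patient lost between t1 and t2 keeps the end-of-intervention value, although the question is the state two months later. Neither is an observed 6-month result, but the model treats both as one.

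The single primary estimate is at stake. It is to be judged against a 12-point difference that the protocol also treats as the clinically meaningful change. If many dropouts are early, the estimate mixes the treatment effect with the dropout rate. If early dropout differs between arms while patients in both arms improve, the arm that loses more patients looks worse for that reason alone. The article states this rule as a positive choice, so it is not a detail left to an analysis plan that is not shown.

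**Working it through.** **The protocol's own figures.** The printed formula is (1.96 + 0.84)² × 2 × 25² × 1.36 / 12² = 7.84 × 2 × 625 × 1.36 / 144 = 92.6. The dropout allowance is 1 − 92.6/120 = 22.8%, printed as 23%. Both reproduce. Whether 92.6 is a total or a per-group number is a separate question; 23% is used here only as the protocol's stated allowance.

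**Inputs from the protocol:** difference of 12 points, dropout 23%, SD 25, ICC 0.04, 12 clusters of 10, visits at t0, 4 and 6 months.

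**Assumed, because the documents do not give them:** timing of dropout, its split between arms, improvement in each arm, share of the effect present at t1, and correlation between visits. Dropout is taken as unrelated to outcome, so that any bias comes from the rule itself.

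**Formula.** Let an arm have true 6-month improvement μ, 4-month improvement ν, dropout d, and share p of its dropouts leaving before t1. The expected improvement after carrying forward is (1 − d) × μ + d × (1 − p) × ν + d × p × 0. The expected estimate is the difference between arms.

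**Equal dropout, 23% in each arm, true effect 12**
- All before t1: 12 × 0.77 = 9.24.
- Half before t1, full effect at t1: 12 × (1 − 0.115) = 10.62.
- None before t1, full effect at t1: 12.0, no bias.
- None before t1, half the effect at t1: 12 × 0.77 + 0.23 × 6 = 10.62.

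**Unequal dropout, all before t1**
- 31% intervention v 15% control, improvement 18 v 6: 18 × 0.69 − 6 × 0.85 = 12.42 − 5.10 = 7.32.
- No true effect, both arms improve by 12, same dropout: 12 × (0.69 − 0.85) = −1.92, a false disadvantage for the intervention. With the split reversed it is +1.92, a false benefit.

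**Precision.** Simulation with 12 clusters of 10, SD 25, ICC 0.04, baseline-adjusted model with a random cluster intercept, 1,500 runs per scenario. With true effect 12, control improvement 5, visit correlation 0.6 and 23% dropout in each arm, all before t1:
- Mean model standard error: 4.08 with carrying forward, 5.01 with observed data only, 4.56 with no dropout at all. The first is 1 − 4.08/5.01 = 19% below the second; at correlations 0.4 and 0.8 the gap is 18%.
- Spread of the carried-forward estimates across runs: 4.03, against the model value of 4.08.
- Coverage of the true 12 points: 92.4% with carrying forward, 96.9% with observed data. With 31% v 15% dropout and a 10-point control improvement, coverage with carrying forward was 81%.
- Rejection under no true effect (both arms improving by 10): 3.5% with equal dropout, 5.1% with 15% v 31%.

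**The case against.** The strongest defence is that carrying forward keeps every randomised patient in the analysis, as intention to treat asks, and errs towards no effect when the arms lose patients alike. Much of this stands. All the equal-dropout figures above lie at or below 12. If dropouts leave after t1 with the full effect reached, there is no bias, and the smaller standard error is earned because t1 carries real information. Power also changes little when dropout is equal: a separate simulation (visit correlation 0.7, cluster-level test, 5,000 runs) gave 61% v 64% for carrying forward against observed data when all leave early, and 65% v 63% when half do. Intention to treat, however, does not require imputed zeros; the alternatives under the fix also keep all randomised patients.

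A reader might infer four stronger things, which the documents do not support.
- *The standard error is invalid and the test too liberal.* It matches the sampling spread of the estimator, and type I error is not inflated under equal dropout. It is too small only as a statement of uncertainty about the true 6-month effect when early zeros are imputed. Inflation needs imbalance: the separate simulation reached 8.1% with 31% v 15% dropout, all early, and a 12-point improvement in both arms, and 6.0% when half were early.
- *The rule contradicts the sample size.* Recruiting extra patients against dropout and then analysing everyone is a cautious allowance, not a contradiction.
- *23% is a forecast.* It is what remains when 92.6 is set against 120.
- *The 4-month DHI has no other use.* The article defines the primary contrast and need not list every analysis of t1.

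The 31% v 15% split is likewise an illustration; nothing in the protocol predicts it.

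**Conclusion.** The point holds in conditional form. The protocol fixes, for its one primary result, a rule that scores early dropouts as unchanged and later ones at their 4-month value. At the protocol's own 23% allowance, split equally, the expected estimate of a true 12-point effect lies between 9.2 and 12, depending on how many leave before t1 and how much of the effect is present by then. With equal dropout the bias is towards the null. With unequal early dropout it can go either way: the illustrations give 7.3 instead of 12, and a false 1.9 points where there is no effect. Neither a fixed direction nor a general failure of the test can be claimed. Because the result depends on quantities unknown in advance, the rule should not carry the primary analysis.

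**What to change.** Replace carrying forward in the primary analysis by one of two methods, fixed before the data are analysed.

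1. A likelihood-based longitudinal mixed model with DHI at t0, t1 and t2 in the outcome vector for all patients. Constrain baseline means to be equal between arms and do not also enter baseline as a covariate. Include group by time, a random intercept for practice, correlated visits within patient, and a small-sample degrees-of-freedom correction for 12 clusters. The group contrast at t2 is the primary effect. Because the protocol's model puts the practice effect on the change, check that a practice-by-visit term is not needed.
2. Alternatively, keep the stated baseline-adjusted model of change and fill in missing t2 values by multiple imputation that respects clustering and includes t1.

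Both assume that data are missing at random given what was observed. Neither needs a further adjustment factor such as region, which the protocol rules out because of the sample size. Keep carrying forward as a sensitivity analysis, beside one that shifts imputed values by a range of amounts separately in each arm. Report dropout by arm and by visit.

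The cost is revised analysis wording, slightly more programming, and a somewhat larger reported standard error. No new data are needed, since t1 is already collected.
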